### Compliance and adverse events monitoring

The PS participants will be provided with a questionnaire on compliance and adverse reactions (in Polish), and will be instructed to record the intake of the supplement, number of stool evacuations, appearance of stools, adverse reactions (gastrointestinal and other), changes in skin lesions, and any medications taken during the trial. At the end of the 8-week intervention, participants will be asked to return the completed questionnaire for compliance assessment.

### Sample size

As the primary outcome is the reduction in the extent and severity of disease determined as change in PASI score from baseline (T0) to T1 in PS patients supplemented with prebiotic ITFs compared with PS patients supplemented with placebo over the 8-week intervention, we assumed a 50% reduction in PASI (PASI50) as being a clinically meaningful improvement in PS treatment [34]. We estimated that 25 evaluable participants in the placebo and prebiotic groups are needed to detect a moderate-to-large between-group difference in PASI change (continuous outcome; standardised difference ≈ 0.8) with 80% power and a two-sided 5% significance level. Given an anticipated dropout rate of 20%, we estimate that 30 participants are required in each randomised study arm to ensure approximately 25 evaluable participants per group at T1. The required number of participants was calculated using the ClinCalc power calculation (clincalc.com) and confirmed with R software. PASI50 will be analysed as a secondary responder endpoint.

### Ethical aspects

The experimental design and procedures were approved by the Bioethics Committee of the Faculty of Medical Sciences at the University of Warmia and Mazury in Olsztyn (Resolution no. 1/2023 of 19 January 2023). The study protocol and all procedures planned in this RCT will be carried out in accordance with the ethical principles set out in the Declaration of Helsinki [35], and ethical and scientific standards of Good Clinical Practice. At the enrolment visit, participants will be informed about the aims, potential risks, and benefits of the planned research and will be asked to sign an informed consent form. Participants will be guaranteed sufficient time to read the study protocol and the informed consent form. If the contents of the documents are not understandable, the research team will clarify any doubts. Participants will be informed that their contribution to the study is voluntary and that they have the right to withdraw at any time. Participants will be assured that all personal data will be anonymised and stored under the GDPR. The study was registered at http://www.clinicaltrials.gov (registration number NCT05971992).

### Statistical analysis plan

The analysis of the results obtained in this RCT with the nutritional intervention will be carried out using the Intention-to-Treat (ITT) approach, providing fair comparisons among the experimental groups, i.e. results of the prebiotic supplemented group will be compared with the results of the placebo group. All randomised participants will be analysed according to the randomisation scheme using all available data. The primary endpoint (change in PASI from T0 to T1) will be analysed using a baseline-adjusted ANCOVA/linear regression model, with treatment group as the main predictor and adjustment for baseline PASI (T0) and the covariates used in covariate-adaptive randomisation (sex, age, BMI). The treatment effect will be reported as an adjusted mean difference with a 95% confidence interval (two-sided α = 0.05). PASI50 will be analysed as a secondary endpoint using logistic regression with the same adjustment set.

Statistical analyses and visualisations will be performed using the R software (www.r-project.org), Statistica 14 software (StatSoft, USA) or GraphPad Prism version 10.0.3 (275) for Windows, GraphPad Software, LLC (Boston, MA, USA). The data within groups will be tested for normality using the Shapiro–Wilk test. Levene’s test will be performed to assess the homogeneity of variances within groups. For secondary outcomes and cross-sectional comparisons, two- or three-group comparisons will be performed using a t-test or ANOVA; if assumptions are not met, alternative nonparametric tests will be conducted (Mann–Whitney or Kruskal–Wallis test). Results will be considered statistically significant when *p* < 0.05. Correlations between selected parameters will be tested using Pearson or Spearman correlation, with prior tests for heteroscedasticity. Logistic and linear regression will be used to estimate associations between parameters. Missing data will be summarised by group with reasons; sensitivity analyses will assess robustness to missingness. Baseline total energy intake and baseline habitual dietary fibre intake from foods (excluding the allocated supplement) will be considered in prespecified sensitivity analyses (and in microbiome association models where relevant) to account for background diet; total fibre intake including the study supplement will not be included as a covariate in the primary efficacy model. For high-dimensional outcomes (e.g., microbiome taxa, metabolomics/VOCs), false discovery rate (Benjamini–Hochberg) control will be applied.

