### Study outcomes

The primary outcome is the between-group difference in the change in PASI score from baseline (T0) to the close-up visit (T1) after the 8-week intervention, which will inform about the change in the severity of skin lesions. The secondary outcomes are changes within and between the prebiotic and placebo group after the 8-week intervention in:

selected clinical parameters,BMI and body composition,nutritional status,resting metabolic rate and respiratory quotient,quality of life,faecal microbiota abundance and diversity,faecal SCFA profile and concentration,level of blood inflammatory cytokines.expression of genes of inflammatory response in skin,level of blood and faecal biomarkers of intestinal barrier permeability;concentration of urine and faecal volatile organic compounds (VOCs).oxidative stress parameters.

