**Table 2 Tab2:**
[figure not shown]
Schedule of enrolment, intervention and assessments [24]

During the enrolment visit (-T_1_), vitals (systolic, diastolic and pulse pressure), body height (stadiometer Seca 213, Seca GmbH & Co, Hamburg, Germany), and body weight (balance Seca 813 Med, Seca GMBH & Co, Hamburg, Germany) were measured in all participants. The body mass index (BMI) was calculated as a ratio of body mass to the square of body height and expressed in kg/m^2^. In addition, a qualified nurse collected a sample (8 mL) of venous blood into a serum vacuum tube (Greiner Bio-One GmbH, Kremsmünster, Austria) to perform a serum IgA antibody against tissue transglutaminase (anti-tTG IgA) assay to rule out gluten-related diseases (e.g., celiac disease) [30]. A dermatologist assessed the severity of skin lesions in PS patients using the Psoriasis Area and Severity Index (PASI).

During the check-up visits T_0_ and T_1_, vitals, anthropometric indices, and body composition will be measured, and an oral glucose tolerance test and metabolic rate evaluation will be performed in all participants after an overnight fast. Additionally, surveys on nutritional status and quality of life will be conducted, and samples of biological materials (blood, urine, urine after SAT, stool, skin) will be collected.

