### Gut microbiota characteristics

The hyper-variable regions of the 16S rRNA bacterial gene (V3-V8) will be amplified with primers 337F 5’- GACTCCTACGGGAGGCWGCAG − 3’ and R1391 5’- GACGGGCGGTGWGTRCA − 3’. Bacterial libraries will be created using a Ligation Sequencing Kit 1D plus either Native Barcoding Expansion or a set of custom barcodes. Final libraries will be sequenced on a GridION X5 sequencer (Oxford Nanopore Technologies, Oxford, UK). All bioinformatic analyses will be performed on the Galaxy Europe platform using publicly available, version-controlled tools. The reads obtained will be filtered for their quality with fastp (v1.0.1 + galaxy2; average read quality ≥ 9 Phred quality score ) and length (minimum 800 bp). During the demultiplexing step, the removal of adapters (crucial for preparing the reads for alignment to a reference genome, as adapter sequences can interfere with alignment accuracy) and barcodes (to ensure that only the actual RNA sequences of interest are retained for each sample, preventing sample contamination) will be performed with Porechop (v0.2.4 + galaxy1). High-quality reads will be processed for taxonomic identification at the genus level by matching the NGS sequences with sequences deposited in the NCBI using Kraken2 (v2.1.3 + galaxy2) and Bracken (v3.1 + galaxy0). Compositional analyses will be performed using total-sum scaling or relative abundances, and multivariate statistics will be applied after centred log-ratio transformation to normalise the data. Alpha diversity will be assessed using the Shannon and Simpson indices, and beta diversity will be evaluated with Bray–Curtis dissimilarity, each with Krakentools (v1.2.1 + galaxy0). Finally, differential abundance will be tested with ANCOM-BC (v1.4.0 + galaxy0) and ALDEx2 (v1.26.0 + galaxy0).

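### Most continuous secondary outcomes get a valid but inefficient unadjusted test although T0 values are collected, and within-arm change is listed as an outcome without being labelled descriptive

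*Protocol article*

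**What the plan says.** All places are in the protocol article.

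- **Outcome definition (Study outcomes):** "The secondary outcomes are changes within and between the prebiotic and placebo group after the 8-week intervention", followed by a list that includes clinical parameters, body composition, quality of life, cytokines, SCFAs, barrier markers and oxidative stress.
- **Test (Statistical analysis plan):** "For secondary outcomes and cross-sectional comparisons, two- or three-group comparisons will be performed using a t-test or ANOVA". Mann–Whitney or Kruskal–Wallis replaces these if assumptions fail. Significance is p < 0.05.
- **Primary outcome (same section):** PASI change "will be analysed using a baseline-adjusted ANCOVA/linear regression model, with treatment group as the main predictor", adjusted for T0 PASI and the randomisation covariates sex, age and BMI.
- **Exceptions:** "PASI50 will be analysed as a secondary endpoint using logistic regression with the same adjustment set". For taxa, "differential abundance will be tested with ANCOM-BC (v1.4.0 + galaxy0) and ALDEx2 (v1.26.0 + galaxy0" (Gut microbiota characteristics).
- **T0 data (Timeline of the study, text after Table 2):** at T0 and T1, "vitals, anthropometric indices, and body composition will be measured, and an oral glucose tolerance test and metabolic rate evaluation will be performed". Questionnaires and biological samples are likewise scheduled for both of these visits.

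**The concern.** The plan accepts the case for baseline and covariate adjustment for PASI and PASI50 but does not carry it over to the other continuous outcomes, which hold the trial's mechanistic evidence. The sample size rests on PASI alone, at a standardised difference of about 0.8, so the secondary outcomes have no stated power in reserve. A more precise analysis is available from data that will be collected anyway.

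The second issue is the word for within-arm change in the outcome definition. A change within one arm mixes any ITF effect with regression to the mean, season and placebo response, and a p-value for it does not compare ITF with placebo. Without a label saying how such changes will be used, a report could set a significant change in one arm against a non-significant change in the other and present the contrast as evidence.

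**Working it through.** **1. The plan's own figure.** Inputs from Sample size: standardised difference 0.8, 80% power, two-sided 5%, 25 evaluable and 30 randomised per arm, 20% dropout.

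n per arm = 2(1.960 + 0.842)² / 0.8² = 24.5, so 25. The t-distribution gives 79.1% power at 25 and 80.7% at 26. The stated figure reproduces. Thirty randomised less 20% leaves 30 × 0.8 = 24 evaluable, and the checks below use 24.

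**2. Power of the three between-arm analyses.** The documents give no T0–T1 correlation r and no effect size for secondary outcomes. Assumptions: a true difference of 0.6 SD and r = 0.3, 0.5 or 0.7. Equal outcome variance at T0 and T1 is also assumed.

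Residual variance v, in units of the outcome variance:
- t-test on T1 values: v = 1
- t-test on change: v = 2(1 − r)
- ANCOVA with the T0 value: v = 1 − r²

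Noncentrality = (0.6/√v) × √(24/2), 46 degrees of freedom, two-sided 5%. Example for r = 0.5: with v = 1 it is 0.6 × 3.464 = 2.08 (power 53%); with v = 0.75 it is 0.6/0.866 × 3.464 = 2.40 (power 65%).

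| r | T1 only | Change | ANCOVA |
|---|---|---|---|
| 0.3 | 53% | 41% | 57% |
| 0.5 | 53% | 53% | 65% |
| 0.7 | 53% | 75% | 81% |

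Charging ANCOVA further degrees of freedom for sex, age and BMI lowers its power by about 0.2 points. ANCOVA leads in every row. Its gain is 4 to 28 points over T1 only and 6 to 16 points over change. The choice between T1 and change, which the plan leaves open, alone moves power by up to 22 points (53% against 75% at r = 0.7).

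**3. What within-arm p-values would do if used as evidence.** Assume both arms change by the same amount c, in SDs of the change score, so there is no ITF effect. Let p be the power of a paired t-test with n = 24 and noncentrality c√24. The arms are independent, so the chance that ITF is significant and placebo is not is p(1 − p).

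| c | p | p(1 − p) |
|---|---|---|
| 0.1 | 8% | 7% |
| 0.2 | 16% | 13% |
| 0.3 | 29% | 21% |
| 0.4 | 47% | 25% |
| 0.5 | 65% | 23% |
| 0.6 | 80% | 16% |
| 0.8 | 96% | 4% |

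The range is about 4% to 25%. The upper end is the mathematical ceiling of p(1 − p), reached near c = 0.4. A between-arm test at two-sided 5% would wrongly favour ITF in 2.5% of trials.

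**The case against.** The strongest reply is that nothing here is invalid. An unadjusted between-arm comparison in a randomised trial is unbiased, and ignoring covariates that steered the allocation tends to make it conservative. The confirmatory analysis already uses ANCOVA, and no power is claimed for secondary outcomes, so no stated figure fails. All of that stands, and it makes this an improvement and not the correction of an error.

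Four stronger readings are tempting, and the documents do not support them.

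- **That the named tests ignore T0.** The outcomes are defined as changes, so a t-test on change is a natural reading, and it does use T0. What can be said is that there is no adjustment and that the quantity compared is not stated. Against a change-score test the gain is the smaller one.
- **That the plan tests within arms.** It lists within-arm change as an outcome but prescribes only group comparisons, and the same section names prebiotic against placebo as the contrast.
- **That an unpaired test will be run on T0/T1 pairs.** The text says nothing of the kind. Leaving a paired test unnamed is a detail that a condensed article may omit.
- **That every secondary outcome is affected.** PASI50 has the full adjustment set, and taxa have their own methods.

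On the other side, the article's brevity does not answer the main point, because its analysis section does name the tests. Its mention of linear regression concerns associations between parameters and is not assigned to treatment effects.

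**Conclusion.** The point holds as a matter of efficiency and clarity. For the continuous secondary outcomes other than taxa, the plan names a valid but less precise test than the one it already uses for PASI, and it leaves open whether T1 values or changes are compared. The size depends on assumptions that the documents cannot settle: at 24 per arm and 0.6 SD, ANCOVA gains 4 points (r = 0.3), 12 points (r = 0.5) or 6 points (r = 0.7) over the better of the two unadjusted tests, and up to 28 points over the worse.

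The within-arm wording is a risk and not a stated intention. The 4% to 25% range applies only if within-arm p-values are computed and read as an ITF effect, with equal changes of 0.1 to 0.8 SD in both arms.

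**What to change.** In the Statistical analysis plan section, analyse each continuous secondary outcome with the primary model: T1 value or change on arm, T0 value of the same outcome, sex, age and BMI. With T0 in the model, T1 and change give the same treatment estimate, so this also settles the open choice. Fix a log scale in advance for right-skewed biomarkers. Report the adjusted between-arm difference with its 95% confidence interval.

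Keep ANCOM-BC and ALDEx2 for taxa, the adjusted logistic model for PASI50, and t-test, ANOVA or rank tests for the cross-sectional comparison with healthy controls.

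In Study outcomes, label within-arm change as descriptive and report it without p-values.

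The cost is wording in two sections. No further data, visits or participants are needed.

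### Unequal variances send secondary and cross-sectional comparisons to rank tests, which do not remedy unequal variances; Welch's test should be the default

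*Protocol article*

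**What the plan says.** Under Study outcomes, the protocol article frames the secondary endpoints as a question about change: "The secondary outcomes are changes within and between the prebiotic and placebo group after the 8-week intervention".

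Under Statistical analysis plan it sets two checks: "The data within groups will be tested for normality using the Shapiro–Wilk test" and "Levene’s test will be performed to assess the homogeneity of variances within groups". (Levene's test compares variances between groups, and I read the sentence that way.) The tests follow: "For secondary outcomes and cross-sectional comparisons, two- or three-group comparisons will be performed using a t-test or ANOVA", and then "if assumptions are not met, alternative nonparametric tests will be conducted (Mann–Whitney or Kruskal–Wallis test". No Welch or robust-variance option is named. The level at which a check counts as failed is not given.

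Three analyses lie outside this rule. The primary PASI change uses a baseline-adjusted linear model and PASI50 uses logistic regression (Statistical analysis plan). Differential abundance of taxa uses ANCOM-BC and ALDEx2 (Gut microbiota characteristics).

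**The concern.** The reference distribution of Mann–Whitney and Kruskal–Wallis comes from treating all observations as exchangeable between groups, so under the null the groups share location, spread and shape. A rejection by Levene's test is evidence against that null. Moving to a rank test at that point leaves the failed assumption in place and changes the hypothesis from a difference in mean change to a difference in distribution. The hypothesis then varies from outcome to outcome with the pretest result.

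Two separate things are at stake:

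- **Error rate.** When spreads differ and group sizes differ, the rank test no longer holds its nominal level.
- **Power.** If only some patients respond to the supplement, the responders themselves widen and skew the prebiotic arm. That trips the checks and moves the analysis to a test that gives less weight to a large effect in a minority.

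A rank-test p-value also supplies no mean difference to set beside the primary result.

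**Working it through.** **Inputs from the protocol article.** 25 evaluable per arm ("We estimated that 25 evaluable participants in the placebo and prebiotic groups are needed", Sample size), equal allocation (Study design) and a 5% significance level (Statistical analysis plan). The planned size reproduces: n = 2(1.960 + 0.842)² / 0.8² = 2 × 7.85 / 0.64 = 24.5, so 25 per arm. The t-based calculation gives 26, with 79.1% power at 25. This figure concerns the primary outcome and is used here only to set the arm size. The article gives no error rate or power for the secondary rule.

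**Assumptions.** Each pretest is run at 0.05, with Levene's test centred at the median. The rule is: Mann–Whitney if Shapiro–Wilk rejects in either arm or Levene rejects, otherwise the pooled t-test. SD ratios, responder shares and response sizes are assumed because the article gives none. Each scenario used 4,000–6,000 simulated trials, so the simulation standard error near 5% is at most √(0.05 × 0.95 / 4000) = 0.34 points. Only two-group comparisons were simulated. The extension to ANOVA and Kruskal–Wallis rests on the same argument.

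**Step 1: false rejection, normal data, equal means**

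| Group sizes | SD ratio | Rule | Welch |
|---|---|---|---|
| 25 v 25 | 1 | 5.1% | 5.1% |
| 25 v 25 | 2 | 5.6% | 5.1% |
| 25 v 25 | 3 | 6.4% | 4.8% |
| 25 v 25 | 4 | 7.0% | 5.0% |
| 30 v 20, larger SD in the 20 | 2 | 7.9% | 5.4% |
| 30 v 20, larger SD in the 20 | 3 | 9.0% | 5.3% |
| 50 v 25, larger SD in the 25 | 3 | 10.6% | 5.4% |
| 20 v 30, larger SD in the 30 | 2 | 3.7% | 4.9% |
| 20 v 30, larger SD in the 30 | 3 | 4.9% | 5.6% |

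With a 2:1 split and the larger SD in the larger group, the rule falls to about 3%. With identical skewed (log-normal) distributions in both arms, meaning no effect of any kind, it gives 5.1%.

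A 20 v 30 split means losing 10 of 30 in one arm and none in the other. That is 10/60 = 17% overall, within the anticipated 20% dropout but split as unevenly as possible. The 50 v 25 case stands for a comparison with the healthy group, whose size is not stated.

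**Step 2: why responders trip the switch.** If a share p of one arm shifts by s SD, that arm's variance is 1 + p(1 − p)s². For p = 0.3 and s = 3 it is 1 + 0.21 × 9 = 2.89, an SD 1.70 times that of placebo. For p = 0.3 and s = 2 it is 1 + 0.21 × 4 = 1.84, an SD ratio of 1.36. At s = 3 with 20–40% responding, about 60–86% of simulated trials switched to Mann–Whitney.

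**Step 3: power, 25 per arm, normal noise**

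| Responders | Shift | Rule | Welch | Loss (points) |
|---|---|---|---|---|
| 20% | 3 SD | 24.1% | 33.1% | 9.0 |
| 30% | 3 SD | 45.5% | 60.6% | 15.1 |
| 40% | 3 SD | 66.7% | 82.1% | 15.4 |
| 30% | 2 SD | 37.6% | 41.2% | 3.6 |
| 30% | 1.5 SD | 27.3% | 28.0% | 0.7 |

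A separate run of the 3 SD cases gave 24%, 45% and 68% under the rule, against 34%, 61% and 84% with Welch.

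**Step 4: cases where the rank test wins.** The rule beat raw-scale Welch for a 1.8-fold log-normal effect (68.6% v 58.5%). It also won for heavy-tailed (t with 3 degrees of freedom) noise with half the patients responding by 2 SD (58.0% v 51.8%), and for a one-unit shift of everyone under the same noise (75% v 61%).

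**The case against.** The strongest reply is that the planned randomised comparison has equal arms, where the rule's error is 5–7% even at a four-fold SD ratio, and that a supplement without effect leaves both arms with one distribution and the rule at 5%. This stands.

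A reader might go further and infer that the rule over-rejects in general, pointing to skewed markers. Log-normal levels with equal arithmetic means and log-SDs of 0.5 v 0.8 or 0.5 v 1.0 give about 17% and 35% rejection. The documents do not support that reading:

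- In those scenarios the medians differ by exp((0.64 − 0.25)/2) = 1.22-fold and exp((1 − 0.25)/2) = 1.45-fold. Welch on the log scale, the natural analysis for such markers, rejects just as often (17.3% and 36.5%). These are real location differences on that scale.
- The secondary outcomes are changes. Changes in log-normal markers with no mean change (assumed log-scale correlation between visits 0.6) gave 5.3–6.0% under the rule.
- Re-centring a 4 SD response in 25% of patients to equal means gives 14–16%, but the other three-quarters must then move 0.25 × 4 = 1 SD the opposite way. That is more than a difference in spread.

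Nor do over-rejection and power loss occur together. The first needs equal means and the second a real mean benefit.

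It is also fair that rank tests can be clearly stronger for heavy tails, so abolishing them would be a poor trade. The either-check-at-0.05 trigger is an assumption. A condensed article may leave transformations and test details to a fuller plan. But this article does more than stay silent: it names the variance check and names rank tests as the response to failed assumptions. That pairing remains wrong.

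**Conclusion.** The concern holds in a limited form. A failed variance check should not lead to a rank test, because that test shares the failed assumption. For equal arms and symmetric changes the excess error is small (about 5–7%). It becomes material, about 8–11% against about 5% with Welch, when groups are unequal and the smaller one is the more variable, at SD ratios of 2–3. Uneven dropout or comparisons with healthy controls could produce that. The opposite pattern makes the rule conservative.

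The power loss is a separate risk. It is about 9–15 points if 20–40% of patients respond by 3 SD, about 4 points at 2 SD, and close to nil at 1.5 SD. These figures rest on assumed response patterns and pretest levels.

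Severity is low to moderate. Only secondary and cross-sectional comparisons are touched, and nothing here affects the primary PASI analysis, PASI50 or differential taxon abundance.

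**What to change.** In the Statistical analysis plan section:

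- Remove Levene's test as a trigger for rank tests. Make Welch's t-test or Welch's ANOVA the default for between-group secondary and cross-sectional comparisons, with no variance pretest. A baseline-adjusted linear model with robust standard errors would serve equally.
- For positive, right-skewed markers such as cytokines, SCFAs, ELISA markers and VOCs, fix log transformation in advance.
- Keep Mann–Whitney and Kruskal–Wallis for markedly non-normal outcomes, or as a labelled sensitivity analysis described as a test of distributional shift.

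The cost is a few sentences before analysis. Even if a normality-based route to rank tests remains, sending unequal variances to Welch brings error to about 5–6% in the normal, unequal-group cases and regains about 3–9 points of power in the responder cases. With equal variances the power loss is negligible. For heavy-tailed outcomes Welch can be clearly weaker than a rank test, which is why the rank test is kept there.
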